### **10.2.2 Independent Data Monitoring Committee (IDMC)**

This study will establish an Independent Data Monitoring Committee (IDMC). In the data review meeting of interim analysis, the safety and efficacy of subjects will be evaluated. At the same time, the IDMC will suggest the time point for the final analysis and provide formal recommendations regarding whether to continue or

terminate the study. This committee will include 2 independent oncologists, 1 independent statistician, and 1 chairman. The IDMC review meeting will be held periodically according to the charter of the IDMC. The study enrollment will continue during IDMC meetings. After the data review, the IDMC will provide suggestions on the time point of the final analysis, whether to continue the study, whether to modify the protocol or whether to discontinue the study.

## Appendix A Study Plan

| ● Randomized treatment study plan        |                  |                  |          |                        |               |                  |                                          |                                        |
|------------------------------------------|------------------|------------------|----------|------------------------|---------------|------------------|------------------------------------------|----------------------------------------|
| Visit                                    | Screening period | Treatment period |          |                        | EOT follow-up | Follow-up period |                                          |                                        |
|                                          | 1                | 2                | 3-7      | 8+                     |               | 28-day follow-up | Progression follow-up once every 6 weeks | Survival follow-up once every 3 months |
| Treatment cycle/Day                      |                  | C1 D1            | C2-C6 D1 | C7 +, every 6 weeks D1 | NA            | NA               | NA                                       | NA                                     |
| Day                                      | -28              | 1                | 22-126   | 127+                   | NA            | NA               | NA                                       | NA                                     |
| Time window (days)                       | NA               | 0                | ± 7      | ± 7                    | ± 7           | ± 7              | ± 7                                      | ± 7                                    |
| Informed consent                         | ×                |                  |          |                        |               |                  |                                          |                                        |
| Demographic and baseline characteristics | ×                |                  |          |                        |               |                  |                                          |                                        |
| Medical/Surgical history                 | ×                |                  |          |                        |               |                  |                                          |                                        |
| Inclusion/Exclusion criteria             | ×                |                  |          |                        |               |                  |                                          |                                        |
| EGFR mutation detection           | ×                |                  |          |                        |               |                  |                                          |                                        |

| ● Randomized treatment study plan            |                  |                  |             |                              |               |                  |                                          |                                        |
|----------------------------------------------|------------------|------------------|-------------|------------------------------|---------------|------------------|------------------------------------------|----------------------------------------|
| Visit                                        | Screening period | Treatment period |             |                              | EOT follow-up | Follow-up period |                                          |                                        |
|                                              | 1                | 2                | 3-7         | 8+                           |               | 28-day follow-up | Progression follow-up once every 6 weeks | Survival follow-up once every 3 months |
| Treatment cycle/Day                          |                  | C1
D1         | C2-C6
D1 | C7 +,
every 6 weeks
D1 | NA            | NA               | NA                                       | NA                                     |
| Day                                          | -28              | 1                | 22-126      | 127+                         | NA            | NA               | NA                                       | NA                                     |
| Time window (days)                           | NA               | 0                | ± 7         | ± 7                          | ± 7           | ± 7              | ± 7                                      | ± 7                                    |
| Physical examination (including body weight) | ×                | ×                | ×           | ×                            | ×             |                  |                                          |                                        |
| Height                                       | ×                |                  |             |                              |               |                  |                                          |                                        |
| ECOG PS Score                                | ×                | ×                | ×           | ×                            | ×             |                  | ×                                        |                                        |
| Pregnancy test                               | ×                |                  |             |                              |               |                  |                                          |                                        |
| Vital signs                                  | ×                | ×                | ×           | ×                            | ×             |                  |                                          |                                        |
| Clinical biochemistry/Hematology/Urinalysis  | ×                | ×                | ×           | ×                            | ×             |                  |                                          |                                        |

| ● Randomized treatment study plan |                  |                                                                               |             |                              |               |                  |                                          |                                        |
|-----------------------------------|------------------|-------------------------------------------------------------------------------|-------------|------------------------------|---------------|------------------|------------------------------------------|----------------------------------------|
| Visit                             | Screening period | Treatment period                                                              |             |                              | EOT follow-up | Follow-up period |                                          |                                        |
|                                   | 1                | 2                                                                             | 3-7         | 8+                           |               | 28-day follow-up | Progression follow-up once every 6 weeks | Survival follow-up once every 3 months |
| Treatment cycle/Day               |                  | C1
D1                                                                      | C2-C6
D1 | C7 +,
every 6 weeks
D1 | NA            | NA               | NA                                       | NA                                     |
| Day                               | -28              | 1                                                                             | 22-126      | 127+                         | NA            | NA               | NA                                       | NA                                     |
| Time window (days)                | NA               | 0                                                                             | ± 7         | ± 7                          | ± 7           | ± 7              | ± 7                                      | ± 7                                    |
| ECG                               | ×                | ×                                                                             | ×           | ×                            | ×             |                  |                                          |                                        |
| Creatine phosphokinase (CK)       | ×                | as clinically necessary                                                       |             |                              |               |                  |                                          |                                        |
| Echocardiography (LVEF)           | ×                | Once every 12 weeks beginning with the first dose, and when clinically needed |             |                              | ×             |                  |                                          |                                        |
| Tumor assessment (RECIST v1.1)    | ×                | Once every 6 weeks after randomization                                        |             |                              |               |                  |                                          |                                        |
| CNS assessment (RECIST v1.1)      | ×                | Once every 6 weeks after randomization in patients with CNS metastases        |             |                              |               |                  |                                          |                                        |

| ● Randomized treatment study plan     |                                                                                      |                  |          |                        |               |                        |                                          |                                        |
|---------------------------------------|--------------------------------------------------------------------------------------|------------------|----------|------------------------|---------------|------------------------|------------------------------------------|----------------------------------------|
| Visit                                 | Screening period                                                                     | Treatment period |          |                        | EOT follow-up | Follow-up period       |                                          |                                        |
|                                       | 1                                                                                    | 2                | 3-7      | 8+                     |               | 28-day follow-up       | Progression follow-up once every 6 weeks | Survival follow-up once every 3 months |
| Treatment cycle/Day                   |                                                                                      | C1 D1            | C2-C6 D1 | C7 +, every 6 weeks D1 | NA            | NA                     | NA                                       | NA                                     |
| Day                                   | -28                                                                                  | 1                | 22-126   | 127+                   | NA            | NA                     | NA                                       | NA                                     |
| Time window (days)                    | NA                                                                                   | 0                | ± 7      | ± 7                    | ± 7           | ± 7                    | ± 7                                      | ± 7                                    |
| Aumolertinib administration           |                                                                                      | ✕ 110 mg, QD     |          |                        |               |                        |                                          |                                        |
| Apatinib administration               |                                                                                      | ✕ 250 mg, QD     |          |                        |               |                        |                                          |                                        |
| Concomitant medication                | [figure not shown] |                  |          |                        |               | ✕ 30 days of follow-up |                                          |                                        |
| Adverse event                         | [figure not shown] |                  |          |                        |               |                        |                                          |                                        |
| Anti-tumor treatment                  | ✕                                                                                    |                  |          |                        |               |                        | ✕                                        | ✕                                      |
| Subsequent response /progression data |                                                                                      |                  |          |                        |               |                        | ✕                                        |                                        |

| ● Randomized treatment study plan |                  |                  |             |                              |               |                  |                                          |                                        |
|-----------------------------------|------------------|------------------|-------------|------------------------------|---------------|------------------|------------------------------------------|----------------------------------------|
| Visit                             | Screening period | Treatment period |             |                              | EOT follow-up | Follow-up period |                                          |                                        |
|                                   | 1                | 2                | 3-7         | 8+                           |               | 28-day follow-up | Progression follow-up once every 6 weeks | Survival follow-up once every 3 months |
| Treatment cycle/Day               |                  | C1
D1         | C2-C6
D1 | C7 +,
every 6 weeks
D1 | NA            | NA               | NA                                       | NA                                     |
| Day                               | -28              | 1                | 22-126      | 127+                         | NA            | NA               | NA                                       | NA                                     |
| Time window (days)                | NA               | 0                | ± 7         | ± 7                          | ± 7           | ± 7              | ± 7                                      | ± 7                                    |
| Survival status                   |                  |                  |             |                              |               |                  |                                          | ×                                      |

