#### **Safety Evaluation:**

Observe and record any adverse events experienced by subjects during the clinical trial period, including clinical symptoms, abnormal vital signs, and abnormal laboratory tests; record severity, time of onset, duration, treatment method, and prognosis; and determine its relatedness to the study drug. Safety endpoints: Occurrence of adverse events; occurrence of serious adverse events; proportion of dose modification, patients withdrawn or due to adverse events.

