A total of 26 patients were included in the phase I dose escalation trial of aumolertinib. No dose limiting toxicity (DLT) occurred in the low-dose group (55/110mg), only 1 of 6 patients in the 220mg dose group had DLT (grade 3 anemia), and only 1 of 6 patients in the 260mg dose group had DLT, grade 3 creatinine elevation; The maximum tolerated dose (MTD) was not reached in the dose escalation phase. Overall objective response rate (ORR) and disease control rate (DCR) were 52.4% and 85.7% for patients eligible for interim evaluation (n=21). In the 55mg (6 cases) and 110mg (6 cases) dose groups, the ORR was 66.7% and DCR was 100.0%. In the 220mg dose group (6 cases), ORR was 50.0%, DCR was 83.3%, and in the 260mg dose group, only 3 cases completed treatment response assessment, DCR was 33.3%.

The Phase I extension study of aumolertinib has completed enrollment in a T790M mutation-positive population, with a total of 91 participants enrolled in the 55mg (30 cases), 110mg (30 cases), and 220mg (31 cases) dose groups. In terms of safety, the common adverse events (AEs) was rash, fatigue, blurred vision, decreased white blood cells, gastrointestinal symptoms (such as constipation, diarrhea, nausea), and elevated levels of creatine kinase and alanine aminotransferase. However, symptoms were mild or asymptomatic, and most AEs resolved on their own. No drug-related serious AEs (SAEs) occurred in the 55mg and 110mg dose groups. In the 220mg dose group, the incidence and severity of AE increased significantly. In terms

of treatment response, among patients eligible for interim evaluation (n=76), overall ORR was 50.0% and DCR was 92.1%. In the 55mg dose group (30 cases), ORR was 53.3% and DCR was 83.3%. The ORR and DCR of 110mg (30 cases) were 46.7% and 96.7% respectively. In the 220mg dose group (16 cases), ORR was 50.0% and DCR was 100.0%.

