The data of 55mg and 110mg in the dose escalation phase and the extension phase were combined for analysis: In the phase I clinical trial of the second-line treatment of advanced NSCLC, 36 patients with T790M mutation-positive were enrolled in the 55mg and 110mg dose groups respectively, and the last patient was followed up for 3 months after enrollment. All patients had been evaluated for efficacy at least twice. At present, there are no unintended safety concerns in either dose group. The overall ORR for T790M mutation was 52.1%, 55.6% in the 55mg dose group and 50.0% in the 110mg dose group. The overall DCR was 92.6%, including 86.1% in the 55mg dose group and 97.2% in the 110mg dose group.

The results of the Phase II single-arm clinical study of aumolertinib were announced at the 2019 World Congress on Lung Cancer (WCLC). The study enrolled 244 patients with locally advanced or metastatic NSCLC with *EGFR* T790M mutation, as well as asymptomatic BMS, and showed an ORR of 68.4%, DCR was 93.4%; The 12-month progression-free survival rate was 53%. Aumolertinib was well tolerated, and the most common adverse events were elevated of creatine phosphokinase, rash, pruritus, elevated of AST/ ALT, anemia, and decreased white blood cell count. Grade 3 or higher drug-related adverse events occurred in 20.9% patients, and no interstitial pneumonia was reported.

In addition, the randomized, double-blind, controlled phase III clinical study of aumolertinib versus gefitinib in first-line treatment of advanced NSCLC with *EGFR* mutations (NCT03849768) is ongoing, with enrollment of 350 participants completed in October 2019, and the primary endpoint reached statistically significant positive results. Specific data will also be presented at international academic conferences in

due course.

Aumolertinib ® (Aumolertinib mesylate tablet) is a class 1 innovative drug independently developed by Jiangsu Hansoh Pharmaceutical Group Co., LTD., and has been approved by the National Medical Products Administration (NMPA) on March 18 (approval number: H20200004) for the treatment of "adult subjects with locally advanced or metastatic NSCLC who have experienced disease progression during or after prior treatment with EGFR-TKI and have been tested positive for *EGFR* T790M mutation."

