## 6. Sample Size

This is a multicenter, randomized, open-label study with a superiority design. The primary endpoint is 18-month PFS rate. Based on the assumptions of 18-month PFS rate of 75% for aumolertinib plus apatinib and 50% for aumolertinib alone, a drop-out rate of 10%, at the significance level of 0.05, to achieve the power of 0.8, a

total number of 98 subjects are needed (49 per arm).

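### After screening, creatine kinase is tested only at the investigator's discretion, so its incidence will probably be under-counted and its comparison between the open-label arms is open to possible detection bias

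*Protocol*

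**What the plan says.** Appendix A (Study Plan) gives CK its own row. It has a cross at screening, the entry "as clinically necessary" across the treatment period, and an empty cell at end of treatment. No other section sets a CK measurement after screening.

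The neighbouring safety rows are built differently. "Clinical biochemistry/Hematology/Urinalysis" and ECG are marked at screening, at every treatment visit and at end of treatment. Echocardiography has a fixed 12-weekly schedule, extra tests when needed, and a cross at end of treatment.

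Section 4.2 says of the 244-patient phase II study of aumolertinib that "the most common adverse events were elevated of creatine phosphokinase, rash, pruritus, elevated of AST/ ALT, anemia, and decreased white blood cell count". For the phase I extension it again names "elevated levels of creatine kinase and alanine aminotransferase" among the common events, and adds of those events as a group that "symptoms were mild or asymptomatic, and most AEs resolved on their own".

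Safety is a secondary endpoint (section 5). The synopsis, under Safety Evaluation, has adverse events recorded "including clinical symptoms, abnormal vital signs, and abnormal laboratory tests". Section 10.2.1 summarises treatment-emergent events by treatment group, overall and by preferred term. On blinding, section 6 states: "This is a multicenter, randomized, open-label study with a superiority design".

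**The concern.** A raised CK without symptoms is found only if someone orders the test. Under this schedule the order depends on clinical judgement, and the person judging knows the arm. The recorded number of CK events is then partly a count of how often patients were tested.

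Two consequences need to be kept apart. The first is under-counting, which follows whenever elevations go untested, in either arm. The second is a distorted difference between arms, which arises only if the arms are tested to different extents.

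What is at stake is the rate of one laboratory event that the protocol itself names as common, together with the adverse event totals it feeds (any event, treatment-related, grade 3 or higher). A statistical analysis plan cannot repair this, because it cannot recover samples that were never tested.

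**Working it through.** The protocol states no CK rate and no testing rate, so there is no figure to reproduce. The check has two parts.

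**1. The passages side by side.**

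- Section 4.2 names CK elevation as a common event in both earlier aumolertinib studies that it describes for safety, and the common phase I events were mild or asymptomatic.
- The synopsis counts abnormal laboratory results as adverse events.
- Section 10.2.1 reports adverse events by arm.
- Appendix A fixes other laboratory tests and ECG by visit, and combines scheduled with as-needed testing for echocardiography. For CK only the as-needed half is present.
- The contents of the biochemistry panel are not listed. A separate CK row suggests that CK lies outside it. If CK is in the panel, the two rows conflict and need reconciling anyway.

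**2. Size, by illustration only.** Let *p* be the true proportion with CK elevation, assumed equal in both arms, and let *t* be the probability of being tested while CK is raised. Then observed rate = *p* × *t*. The values of *p* and *t* below are assumptions. The 49 patients per arm come from section 6.

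The chance of a false significant difference uses a two-sided 0.05 pooled two-proportion test, which is equivalent to the uncorrected chi-square test that section 10 names for categorical variables. With *a* = *p* × *t*₁, *b* = *p* × *t*₂, *d* = |*a* − *b*| and *m* = (*a* + *b*)/2:

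- SE₀ = √(2*m*(1 − *m*)/49)
- SE₁ = √((*a*(1 − *a*) + *b*(1 − *b*))/49)
- chance = Φ((*d* − 1.96 SE₀)/SE₁) + Φ((−*d* − 1.96 SE₀)/SE₁)

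Worked case, *p* = 0.30 with testing 0.7 against 0.5:

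- *a* = 0.30 × 0.7 = 0.21, *b* = 0.30 × 0.5 = 0.15, *d* = 0.06, *m* = 0.18
- SE₀ = √(2 × 0.18 × 0.82/49) = 0.0776
- SE₁ = √((0.21 × 0.79 + 0.15 × 0.85)/49) = 0.0774
- chance = Φ(−1.19) + Φ(−2.74) ≈ 0.12

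Results for *p* = 0.30:

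| Tested while raised, combination / monotherapy | Observed | Difference (points) | Chance of a false significant difference |
|---|---|---|---|
| 1.0 / 1.0 | 30% / 30% | 0 | 5% |
| 0.5 / 0.5 | 15% / 15% | 0 | 5% |
| 0.7 / 0.5 | 21% / 15% | +6 | 12% |
| 0.8 / 0.4 | 24% / 12% | +12 | 34% |
| 0.4 / 0.8 | 12% / 24% | −12 | 34% |

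For assumed true rates of 20% to 40%, the chance runs from 9% to 15% for 0.7 against 0.5, and from 23% to 46% for 0.8 against 0.4. Equal but incomplete testing halves the rate in the second row without biasing the comparison. A false difference appears only when testing differs by arm, and its sign follows whichever arm is tested more.

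**The case against.** The strongest case against is that nothing in the protocol shows that testing will differ by arm. Both arms take aumolertinib 110 mg daily on one visit schedule, and the protocol ties CK elevation to aumolertinib, not to apatinib. Testing could be equally sparse in both arms. Section 10.2.1 plans no specific CK comparison, and the common events mostly resolved without intervention, which offers some reason for discretionary testing. Missed asymptomatic elevations would rarely change the counts of serious events, withdrawals or deaths.

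Much of this stands, and it limits the point. A reader might infer that the safety question cannot be answered for CK without detection bias. The documents do not support that: between-arm bias is possible, not certain. A reader might also infer that CK elevation is the drug's leading laboratory toxicity. That would rest only on the order of a list. No rates are given, and the phase I list names decreased white blood cells before CK. The description of events as mild or asymptomatic covers the common phase I events as a group and is not specific to CK.

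What the objection does not remove is the probable under-count. Nor does it supply any safeguard against arm-aware testing. Section 7.1 states a general aim of comparing safety between the regimens, and preferred-term tables by arm will set the two CK rates next to each other whether or not a test is planned.

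**Conclusion.** The point holds in a limited form. Followed as written, the CK row will probably under-count CK elevation in both arms and leaves the between-arm comparison open to detection bias of unknown size and direction. Under-counting assumes that some elevations go untested, which is likely where symptoms are absent. Bias between arms further assumes that testing differs by arm, which the protocol neither shows nor prevents. The numerical examples are illustrations, not estimates.

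The effect is confined to one laboratory event, and the adverse event counts it enters, within a secondary endpoint. The primary endpoint is unaffected. This is a cheap improvement worth making, not a threat to the trial's main conclusion.

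**What to change.** Reconcile the CK row in Appendix A with the safety endpoint. Measure CK on the biochemistry sample already scheduled in both arms: C1D1, day 1 of C2 to C6, every 6 weeks from C7, and end of treatment. Keep unscheduled tests as additional, and base the between-arm CK summary on the scheduled samples. If the schedule is left as it is, state in the protocol that CK elevation rates are not comparable between arms.

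This concerns ascertainment of the endpoint only and implies no dose or management rule. The cost is one analyte on blood already drawn, with no extra visit or procedure. The downside is a small laboratory cost and more asymptomatic CK elevations reported as adverse events.
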